**Primary endpoint:**

This study will implement a waitlist control Randomised Controlled Trial design, where participants will be randomly assigned to active treatment (DWM) or a waitlist control condition (WL) on a 2:1 ratio.

The main study parameter will be psychological distress, measured using the Kessler Psychological Distress Scale – 10-item version (K10; Kessler et al., 2002). A description of this measure can be found under “Measurement Instruments”. This measure is administered at pre-treatment (including as a screening measure), mid-treatment, immediately post-treatment, and 1 month after the completion of treatment.

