# **Safety and Monitoring**

1. Assessment of Safety Event Report Forms

Safety reports will be assessed on the seriousness, causality, and expectedness of the event to the trial treatment(s), intervention(s), investigational medical product(s), investigational medical device(s). The following are known and expected adverse effects, harms, risks or discomforts associated with trial procedures, treatments or interventions.

1. Known Adverse Effects

There are no known adverse effects associated with this intervention. The DWM intervention is low-intensity and implements present-focused psychological strategies that have been demonstrated to improve mental health. Thus, we do not anticipate any additional risk or burden for participants.

1. Known Harms, Risks or Discomforts

Participants will be asked to respond to interview questions, and complete brief online questions, about their psychological state and mood, physical health, refugee status and their history of stressful events. This procedure may lead to transient psychological distress, however no psychological stress will be placed on participants that they do not normally experience. Administering the instruments is crucial to draw conclusions about the intervention’s efficacy and mechanisms of change. The research team has extensive experience in conducting research with refugees in Indonesia and Australia and the project Assessors have been trained in interview techniques and how to manage negative emotional reactions in participants.

Participants will be in regular contact with the research team throughout the intervention (with Structured Assessments every 3-weeks and regular facilitator calls during the DWM phase). If, at any stage, the participant experiences an undesirable emotional reaction or indicates they are experiencing significant symptoms (i.e., issues in line with our exclusion criteria, such as symptoms consistent with a severe physical or mental condition) then the trained assessor/facilitator will be able to triage the issue by either

(1) providing referral information directly to the participant so they can access more specialised services, or

(2) escalating the participant to the research team's clinical supervisor who can assess and refer as needed.

1. Adverse Events or Adverse Reactions

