Adverse events (AE) are considered any untoward medical occurrence in a patient or clinical trial participant administered the intervention, which does not necessarily have a causal relationship with this treatment.

Adverse Reactions (AR) are considered untoward and unintended responses to the trial intervention related to any intervention procedures.

AEs and ARs are assessed using the safety monitoring flow chart. Those classified as "not serious" are assessed by the qualified physician/medical expert specified in section 2 of the protocol. The Qualified Physician cannot delegate this responsibility to other research personnel.

Adverse event reports must be reported to the Coordinating Principal Investigator without undue delay. All adverse event reports must be recorded in the [UNSW Safety Monitoring Register Template](https://research.unsw.edu.au/document/UNSW%20Safety%20Monitoring%20Register%20Template.xlsx).

1. Serious Adverse Events

Serious Adverse Events (SAEs) that result in or lead to one or more of the following and the event is not related to the trial intervention:

- The death of a trial participant.
- A life-threatening illness or injury involving a trial participant.
- A participant's permanent impairment of body structure or body function.
- In-patient or prolonged hospitalisation (not for a pre-existing condition or an elective surgery) of a trial participant.
- Medical or surgical intervention to prevent life-threatening illness or injury or permanent impairment to a body structure or function of a trial participant.
- Fetal distress, fetal death or congenital abnormality or birth defect.

SAE reports are classified following the safety assessment flowchart and are assessed by Sponsors Independent Medical specified in section 2 of the protocol. The Sponsors Independent Medical cannot delegate this responsibility to other research personnel. SAE reports are reported to the Coordinating Principal Investigator within 48 hours of the event occurring for multicentre clinical trials. SAR reports must be recorded in the [UNSW Safety Monitoring Register Template](https://research.unsw.edu.au/document/UNSW%20Safety%20Monitoring%20Register%20Template.xlsx).

1. Serious Adverse Reactions

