A Serious Adverse Reactions (SAR) is an SAE that is related to the trial intervention. SAR reports are classified following the safety assessment flowchart and are assessed by Sponsors Independent Medical specified in section 2 of the protocol. The sponsors independent medical expert must determine whether the SAR was expected or unexpected. The Sponsors Independent Medical cannot delegate this responsibility to other research personnel.

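### Non-serious adverse events are undefined for the waitlist arm, and the SAE and SAR definitions exclude each other

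*Protocol*

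**What the plan says.** The definitions are all in Section 11 of the protocol, Safety and Monitoring.

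- **AE:** "Adverse events (AE) are considered any untoward medical occurrence in a patient or clinical trial participant administered the intervention". A causal link is not required.
- **SAE:** events that "result in or lead to one or more of the following and the event is not related to the trial intervention". The list that follows is worded for any participant in the trial; its first item is "The death of a trial participant".
- **SAR:** this "is an SAE that is related to the trial intervention".
- **SUSAR:** a serious adverse reaction that was not anticipated. The 7-day and 15-day reporting duties attach to this category.
- **Contact with participants:** the subsection on known harms describes regular contact, "with Structured Assessments every 3-weeks and regular facilitator calls during the DWM phase".
- **Reporting time for SAEs:** "within 48 hours of the event occurring for multicentre clinical trials". The SUSAR times run from awareness of the case.

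On design, "participants will be randomly assigned to active treatment (DWM) or a waitlist control condition (WL) on a 2:1 ratio". The Treatment of Subjects and Trial Intervention sections give waitlist participants the workbook and audio files only after their last assessment, 9 weeks after baseline.

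**The concern.** There are two faults, and both follow from the wording.

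First, the AE definition depends on having been given the intervention. During the randomised period only the DWM arm has been given it. An injury, an illness or a non-serious crisis in a waitlist participant would not meet the definition, whereas the same event in a DWM participant would. Participants enter with raised distress (K10 above 19.9), so some background events are likely. If the definition is followed as written, the non-serious events found under DWM have no control rate to be read against. That matters for the emerging-safety review and the annual safety assessment, both of which Section 11 requires.

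Second, the serious-event categories contradict each other. A SAR is defined as a subset of SAEs, but SAEs have already been limited to unrelated events. A serious event caused by the intervention has no category, and the SUSAR duties rest on one that is empty as worded.

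**Working it through.** **1. Size of the waitlist arm**

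The protocol gives two totals, so both are shown.

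- Sample Size: 303 participants at 2:1, so 303 / 3 = 101 on the waitlist and 202 in DWM.
- Trial Intervention: 214 + 107 = 321, so 107 / 321 = 33.3% on the waitlist.

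The share is one third either way. The printed evaluable arms, 150 and 73, give nearly the same: 73 / 223 = 32.7%.

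**2. Who the AE definition covers during the 9 weeks**

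| | Covered as worded | Covered if worded for all randomised | Difference |
|---|---|---|---|
| Sample Size total | 202 of 303 | 303 of 303 | 101 |
| Trial Intervention total | 214 of 321 | 321 of 321 | 107 |

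As follow-up time with no attrition, this is 101 × 9 / 52 = 17.5 person-years, or 107 × 9 / 52 = 18.5. The protocol expects 35% attrition. If all of those losses came at the start, the smaller figure would fall to 101 × 0.65 × 9 / 52 = 11.4. The range is therefore about 11 to 19 person-years.

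**3. Whether another section fills the gap**

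- The SAE list covers both arms, but only for serious outcomes.
- The instrument table under Measurement Instruments has K10, PCL-6 and SIDAS at Structured Assessments 1 to 4 in both arms. It lists no adverse-event question.
- The rule on undesirable emotional reactions, under known harms, applies in either arm. It is a rule for triage and referral and does not say what is to be recorded as an event.

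None of these brings a non-serious waitlist event within the AE definition.

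**4. The serious-event categories side by side**

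- SAE = serious and not related.
- SAR = SAE and related = serious, not related and related. No event satisfies this.
- SUSAR = SAR and unexpected. It is empty for the same reason.

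**5. Opportunity to hear of events**

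Scheduled live contacts after baseline are 5 calls + 3 assessments = 8 in DWM and 3 on the waitlist, a difference of 5. This counts scheduled live contacts only. The EMA blocks, the prompts after missed surveys and the attempts to rebook missed assessments apply to both arms alike. They raise both totals without removing the difference.

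**The case against.** A reader might infer that harms cannot be compared between the arms at all, or that the trial will hold AE data for one arm only. The documents do not support either statement. The SAE list applies to any trial participant, so serious waitlist events are covered. Worsening distress, PTSD symptoms and suicidal ideation are measured on the same schedule in both arms by assessors blind to allocation. Those scores are not event records, but they do allow comparison of some plausible harms.

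Four further objections carry weight.

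- The protocol promises no between-arm comparison of AEs, and tabulation by arm may properly sit in an analysis plan that is not shown. This is correct. However, the definition itself is in the protocol, and a later table cannot recover events that the definition excluded.
- Much of Section 11 reads like a sponsor template, nothing tells staff to ignore waitlist events, and the classification flow chart is not reproduced in the text available. Practice may therefore be better than the wording. That does not make the wording correct.
- The SAE/SAR contradiction may have little effect in practice. Both categories go to the sponsor's independent medical expert, and all single-case reports enter the register. This limits the consequence, but the expedited SUSAR duties still depend on the SAR category.
- The 48-hour rule is qualified as applying to multicentre trials. The documents available do not establish that this trial is multicentre, so it cannot be said that the rule will be breached. The difference in starting point between the SAE and SUSAR texts is a minor matter of consistency.

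The extra facilitator calls are inherent in comparing guided care with a waitlist. They are a reason to record the source of each event and are not a fault in the design.

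**Conclusion.** The point holds as two defects of wording that should be corrected.

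- Non-serious events in the waitlist arm, one third of participants (101 of 303 or 107 of 321), lie outside the AE definition throughout the 9-week comparison.
- The SAR category, and with it the SUSAR category, is empty as defined.

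The first conclusion assumes that the AE sentence is applied literally and that no operating procedure outside the protocol overrides it. The second needs no assumption beyond reading the definitions together. Serious events and symptom scores are available in both arms, so the loss is confined to non-serious events. The sample size, power and primary analysis are unaffected.

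**What to change.** 1. Reword the AE definition to cover any untoward occurrence in any randomised participant, in either arm, from randomisation to the final assessment.
2. Record events in both arms, in the same way, at Structured Assessments 2 to 4. Mark events first heard in a facilitator call, so that any comparison between arms can rest on the records obtained with equal opportunity.
3. Remove the unrelatedness condition from the SAE definition, so that the SAE, SAR and SUSAR definitions agree.
4. As a minor point, reconcile the start of the SAE reporting period with the awareness-based SUSAR wording, and state whether the multicentre qualifier applies to this trial.

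The cost is one wording amendment, a short addition to assessments already scheduled, and slightly more events to record and classify.

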#### **Expected Serious Adverse Reaction**

A serious adverse reaction by its nature, incidence, severity, or outcome is anticipated and identified in the current version of the intervention safety information are classified as a SAR report. SAR reports are reported to the Coordinating Principal Investigator without undue delay for multicentre clinical trials. Serious Adverse Reaction reports must be recorded in the [UNSW Safety Monitoring Register Template](https://research.unsw.edu.au/document/UNSW%20Safety%20Monitoring%20Register%20Template.xlsx).

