#### **Suspected Unexpected Serious Adverse Reaction (SUSAR)**

A serious adverse reaction by its nature, incidence, severity, or outcome is unanticipated and not identified in the interventions instructions for use or safety information are classified as a SUSAR.

Fatal or life-threatening Australian SUSAR reports are reported to the Coordinating Principal Investigator, the sponsor's delegate and the approving HREC within 7 calendar days after being made aware of the case follow up information reported within a further 8 calendar days.

All other Australian SUSAR reports are to be reported to the Coordinating Principal Investigator, the sponsor's delegate and the approving HREC within 15 calendar days after being made aware of the case follow up information reported within a further 8 calendar days. SUSAR reports must be recorded in the [UNSW Safety Monitoring Register Template](https://research.unsw.edu.au/document/UNSW%20Safety%20Monitoring%20Register%20Template.xlsx).

1. Significant Safety Issue (SSI)

A safety issue that could adversely affect participants' safety or materially impact the trial's continued ethical acceptability or conduct. The Human Research Ethics Committee and Sponsor's Delegate must be notified of all significant safety issues within 15 calendar days of the sponsor instigating or being made aware of the issue**.** SSI reports must be recorded in the [UNSW Safety Monitoring Register Template](https://research.unsw.edu.au/document/UNSW%20Safety%20Monitoring%20Register%20Template.xlsx).

1. Urgent Safety Measure (USM)

A measure that is taken to eliminate an immediate hazard to a participant's health or safety. Significant safety issues where an urgent safety measure is required to be taken to eliminate an immediate hazard must be classified as a significant safety issue requiring an urgent safety measure. The Human Research Ethics Committee and the Sponsor's Delegate must be notified of any significant safety issues that meet the definition of an urgent safety measure should be notified within 72 hours. Examples include:

- a serious adverse event that could be associated with the trial procedures and that requires modification of the conduct of the trial
- a patient population hazard, such as lack of efficacy of an intervention used for the treatment of a life-threatening disease.

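### The protocol defines an SAE as unrelated to the intervention and a SAR as an SAE that is related, so read literally no event can be a SAR or a SUSAR

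*Protocol*

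**What the plan says.** All of this is in the protocol, section 11 (Safety and Monitoring).

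- **Adverse events.** An adverse event is an untoward occurrence "which does not necessarily have a causal relationship with this treatment". Causality plays no part in this definition. Adverse reactions are defined separately, as responses related to the intervention.
- **Serious Adverse Events.** The definition lists serious outcomes (death, life-threatening illness or injury, hospitalisation and others) and requires "one or more of the following and the event is not related to the trial intervention".
- **Serious Adverse Reactions.** A SAR "is an SAE that is related to the trial intervention". The sponsor's independent medical expert decides whether it was expected.
- **SUSAR.** The definition starts from the SAR: "A serious adverse reaction by its nature, incidence, severity, or outcome is unanticipated" and not identified in the safety information.
- **Urgent Safety Measure.** The first example uses the term serious adverse event for an event that may be linked to trial procedures.

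The reporting rules attach to these classes. For SAEs, "SAE reports are reported to the Coordinating Principal Investigator within 48 hours of the event occurring for multicentre clinical trials". For expected SARs, "SAR reports are reported to the Coordinating Principal Investigator without undue delay for multicentre clinical trials". Fatal or life-threatening SUSARs go to the Coordinating Principal Investigator, the sponsor's delegate and "the approving HREC within 7 calendar days after being made aware of the case". Other SUSARs have 15 calendar days.

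**The concern.** The SAE definition carries a causality condition that the next definition reverses. A site that applies the text word for word to a serious event it thinks may be linked to the intervention cannot call it an SAE. It therefore cannot call it a SAR or a SUSAR either.

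Three rules depend on those labels:

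- **Who assesses the event.** Events classed as not serious go to the qualified physician. SAEs and SARs go to the sponsor's independent medical expert. A serious, related event fits none of these categories literally.
- **Whether expectedness is decided.** That step is written for SARs only.
- **Whether the HREC and sponsor's delegate hear of a single case.** The section on reporting safety monitoring reports exempts single AEs, ARs, SAEs and SARs, which go into the register and to the delegate annually. SUSARs are not in that exemption. A wrong label could turn a 7- or 15-day report into a line in an annual register.

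The trial enrols people with a K10 above 19.9 and measures suicidal ideation at every structured assessment, so the definitions of serious events need to be usable.

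**Working it through.** No figure in the protocol bears on this point and no calculation applies. The check is set logic, followed by a comparison of the reporting rules.

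**Definitions.** Let S be a listed serious outcome and R be relatedness to the intervention.

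1. SAE = S and not R (Serious Adverse Events).
2. SAR = SAE and R (Serious Adverse Reactions).
3. Putting 1 into 2: SAR = S and not R and R, which is empty.
4. A SUSAR is a serious adverse reaction that is unanticipated, hence a subset of SAR, hence empty.
5. An event that is S and R is neither SAE nor SAR. Only the general AE/AR text is left for it, with the rule "Adverse event reports must be reported to the Coordinating Principal Investigator without undue delay" and no fixed limit.

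**Consistency with neighbouring text.**

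- The parent AE definition is neutral on causality, so a serious AE would be expected to be neutral too. The SAE definition is not.
- The urgent-safety-measure example calls a possibly related event a serious adverse event. Under step 1 it could not be one if it were related.
- The SAE paragraph ends by telling staff to record SAR reports in the register, so the two classes are also mixed in the working instructions.

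**Reporting rules side by side.**

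- AE: to the Coordinating Principal Investigator, no fixed limit.
- SAE: to the Coordinating Principal Investigator, 48 hours, counted from the event.
- Expected SAR: to the Coordinating Principal Investigator, no fixed limit.
- SUSAR: to the Coordinating Principal Investigator, sponsor's delegate and HREC, 7 or 15 calendar days, counted from awareness.
- Significant safety issue: to the HREC and sponsor's delegate, 15 calendar days.
- Urgent safety measure: to the HREC and sponsor's delegate, 72 hours.

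Two things follow. The last two routes do not use the SAR definition, so they survive the contradiction. And the time to the Coordinating Principal Investigator differs between SAE, expected SAR and SUSAR in both length and starting point. Once the definitions are repaired, a related serious event is both an SAE and a SAR, so more than one of these times would apply to it.

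**The case against.** The strongest reply is that the intended scheme is plain. Section 11 opens by having every report assessed for seriousness, causality and expectedness. Adverse reactions are defined without reference to SAEs, and the rule for those judged not serious implies that some are serious. The expected-SAR and SUSAR paragraphs start from the serious adverse reaction, not from the SAE. On this view unrelated serious events are SAEs, related ones are SARs, and a single linking sentence is badly worded. SAE and SAR reports are also classified by a flow chart that is not shown and may separate the classes correctly.

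This stands as an account of intent, and it limits what can be said about practice. It does not remove the contradiction. If the flow chart is right, it disagrees with the text, and the text still has to be corrected.

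A reader might infer three stronger things, none of which the protocol supports.

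- **That the most important events have the weakest reporting rule.** On the intended reading SUSARs have the widest recipients of any single-case rule. The protocol states that the intervention has no known adverse effects, so most related serious events would be unexpected and take the SUSAR route. A rule without a fixed limit is also not necessarily slower than 48 hours.
- **That related serious events would go unreported.** The significant-safety-issue and urgent-safety-measure routes remain, and the flow chart may direct such events properly.
- **That the results would show no related serious events by construction.** The protocol specifies no SAE table, and it requires SARs and SUSARs to be entered in the register.

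**Conclusion.** The contradiction is real and the SAE definition is wrong as written. Read literally, the SAR and SUSAR classes are both empty, and the expectedness decision and the SUSAR reports to the HREC and sponsor's delegate have nothing to act on. The practical effect is a risk that serious, possibly related events are misclassified. A loss of reporting is not shown.

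The conclusion rests on the text of section 11 alone. It assumes nothing about event rates, and no frequency of misclassification can be given. It does not affect sample size, power or type I error.

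Three matters stay open: what the flow chart shows; whether the SAE and SAR rules, worded for multicentre trials, cover this trial; and whether the SUSAR times, worded for Australian reports, cover events in Greater Jakarta. The conclusion depends on none of them.

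**What to change.** Delete the causality condition at the end of "one or more of the following and the event is not related to the trial intervention", so that an SAE is any listed serious outcome regardless of cause. The SAR then becomes its related subset and the SUSAR the unexpected part of that. This one deletion also removes the conflict with the urgent-safety-measure example and brings the SAE into line with the AE definition. Rewording only the SAR sentence would leave the conflict with the example in place.

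Align the flow chart and the register with the amended definitions, and correct the sentence in the SAE paragraph that refers to SAR reports.

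The sponsor should also reconcile the reporting times to the Coordinating Principal Investigator: 48 hours from the event for SAEs, no fixed limit for expected SARs, and 7 or 15 calendar days from awareness for SUSARs. Which time is right is not judged here.

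The cost is a short protocol amendment with matching edits to the flow chart and register. Correcting the definition needs no new procedure or staff, and no change to the design or analysis.

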# **Selection and Withdrawal of Subjects**

## **Inclusion Criteria**

Inclusion criteria for participants taking part in this study include:

(a) 18+ years,

(b) from a refugee background,

(c) able to speak and read Farsi, and

(d) experiencing elevated levels of psychological distress (K10 > 19.9)

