## **Exclusion Criteria**

Exclusion criteria for those who are not eligible to participate in the study include:

(a) participants that do not meet the above inclusion criteria

(b) acute medical conditions,

(c) imminent suicide risk or with expressed acute needs/protection risks (e.g., a woman who reports that she is at acute risk of domestic and/or sexual

violence),

(d) severe mental disorder (psychotic disorders, substance-dependence),

(e) severe cognitive impairment (e.g., severe intellectual disability or dementia), and/or

(f) concurrent psychological treatment (e.g., currently receiving psychological services from a psychologist, counsellor or mental health-focused program)

(g) no access to a smart phone and internet connection.

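### The SAE hospitalisation criterion does not say that admission for worsening of a pre-existing condition counts, and psychological and protection events are not clearly tied to the reporting rules in both arms

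*Protocol*

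**What the plan says.** Section 11 (Serious Adverse Events) lists six seriousness criteria: death, life-threatening illness or injury, permanent impairment, hospitalisation, intervention to prevent the life-threatening or permanent outcomes, and fetal events. Only hospitalisation carries an exception for the participant's earlier state: "In-patient or prolonged hospitalisation (not for a pre-existing condition or an elective surgery) of a trial participant". The protocol does not define a pre-existing condition and does not mention worsening of one.

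The general definition in the same section is: "Adverse events (AE) are considered any untoward medical occurrence in a patient or clinical trial participant administered the intervention". No causal link is needed.

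Classification decides who looks at the event. Non-serious events go to the qualified physician. SAEs go to the sponsor's independent medical expert and, in wording addressed to multicentre trials, to the coordinating principal investigator within 48 hours. A serious adverse reaction (SAR) is defined as a related SAE. A SUSAR is an unexpected SAR, with expedited reports to the ethics committee at 7 or 15 days.

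On entry, Section 9.1(d) requires participants to be "experiencing elevated levels of psychological distress (K10 > 19.9" or more precisely above that cut-off, and Section 9.2 excludes "imminent suicide risk or with expressed acute needs/protection risks" and "severe mental disorder (psychotic disorders, substance-dependence" among others.

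During the trial, Section 11 (Known Harms, Risks or Discomforts) covers significant symptoms, glossed as "issues in line with our exclusion criteria, such as symptoms consistent with a severe physical or mental condition". The assessor or facilitator triages in one of two ways: "providing referral information directly to the participant so they can access more specialised services", or "escalating the participant to the research team's clinical supervisor who can assess and refer as needed".

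**The concern.** The foreseeable harms in this trial are psychological and social: deterioration, suicidality, emergence of severe disorder, and danger from others. The event definitions are general medical ones. If they classify such events inconsistently, the safety table depends on how individual staff read the wording.

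This matters because the protocol states that the intervention has no known adverse effects, and the Background reports no direct adverse events in earlier trials of this or similar programmes. This trial will add to that record. A low count would reassure only if the rules reliably bring the relevant events into the register, at the right level of seriousness and on the same terms in both arms.

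**Working it through.** The point involves no power, alpha or event-rate calculation. The check sets the provisions side by side.

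**1. The hospitalisation exception against the entry criteria.** Every participant has a K10 score above 19.9 at entry. Suicidal ideation short of imminent risk is not excluded. If someone later deteriorates and is admitted, one reader may call the admission new and another may call it an admission for the condition that qualified the person for the trial. The text supports both readings, and no sentence on worsening decides between them.

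**2. What follows from a non-serious label.** If no other criterion is met, the admission goes to the qualified physician, not to the independent medical expert, and the 48-hour report does not apply. Because a SAR must first be an SAE, and a SUSAR must first be a SAR, the event cannot enter either class even if it is thought to be related to the intervention. Section 11 (Reporting of Clinical Trial Safety Monitoring Reports) leaves single non-serious cases to annual reporting.

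**3. Triage against reporting.** The triage trigger refers to the exclusion criteria, and those include imminent suicide risk and acute protection risk. Neither triage route mentions an event report, the register or the physician. The next subsection requires adverse event reports to be registered, but nothing says that a triage produces a report.

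**4. Which events the text settles.**

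| Event | Where the text puts it | Settled? |
| --- | --- | --- |
| Suicide | SAE: death | Yes |
| Life-threatening attempt or assault injury | SAE: life-threatening illness or injury | Yes |
| Attempt, not life-threatening, no admission, treated participant | Non-serious adverse event | Yes, if reported |
| Psychiatric admission for worsening distress, no other criterion met | SAE or non-serious, by reading of the exception | No |
| Imminent suicide risk emerging at a call or assessment | Triage; adverse event only if someone judges it medical and files a report | No |
| Acute protection risk without injury | Triage; not clearly a medical occurrence | No |
| Non-serious event in a waitlist participant before the final assessment | Adverse event definition refers to participants given the intervention | No |

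**5. The waitlist arm.** Under Section 10, waitlist participants receive the workbook and audio files only after the final assessment at week 9, so during follow-up they have not been given the intervention. With 2:1 allocation they are 1/(2+1) = one third of those randomised: 303/3 = 101 on the Sample Size total, or the 107 stated in Section 10. The SAE criteria speak of trial participants generally, so the doubt is greatest for non-serious events.

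**The case against.** The best reply is that several other provisions catch these events.

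- The general adverse event definition has no exception for pre-existing conditions, so an admission held to be non-serious can still be registered in a treated participant.
- Suicide, dangerous attempts and serious injuries meet criteria that have no exception.
- The adverse reaction definition is not confined to medical events.
- A Significant Safety Issue need not be medical. It must be registered and notified within 15 days, or within 72 hours where an urgent measure is needed.
- Failure to record adverse events is listed in Section 12.2 as an example of a serious breach.
- Suicidal ideation (SIDAS) is measured in both arms at all four structured assessments.
- Triage is a participant-care step that does not displace reporting, and facilitators and assessors are supervised by a clinical psychologist.
- Psychosis and imminent suicide risk are excluded at entry, so an admission for either would ordinarily be new.

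Most of this stands. A reader might infer that these events fit no adverse event category and that the trial's main harms go uncounted. The documents do not support that. A reader might also infer that every participant has, by definition, a pre-existing condition. That is an interpretation of a screening score, not something the protocol states.

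The reply does not remove the ambiguity. None of these provisions says whether admission for worsening is serious, links a triage to a report, or brings waitlist participants within the adverse event definition. SIDAS is analysed as a secondary outcome. It has no stated event threshold or link to the register, and it does not record admissions or protection events.

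**Conclusion.** The point holds as a defect of wording with a real consequence for classification. A psychiatric admission for deterioration that meets no other criterion can be ruled non-serious, and then loses independent medical review and any route to SAR or SUSAR status. Emergent suicide risk short of injury, protection events without injury, and non-serious waitlist events risk going unreported or being captured differently by arm.

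On size, the exception touches one of six seriousness criteria, and the restriction in the adverse event definition puts about one third of participants in doubt. The protocol gives no rate of admissions, suicidal events or protection events, so the number affected cannot be estimated.

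Three assumptions are needed. First, qualifying distress can be read as a pre-existing condition; the text permits this but does not require it. Second, the safety assessment flow chart, a figure not reproduced in the text available, does not settle these routes. Third, the six criteria are meant to serve related and unrelated events alike. Read literally, the SAE paragraph is confined to unrelated events while a SAR is defined as a related SAE, and those two statements also need to be reconciled.

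**What to change.** Make three changes of wording in Section 11:

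1. **Hospitalisation.** Limit the exception to admissions planned before enrolment that do not arise from worsening of the pre-existing condition, so that an admission for worsening counts as serious.
2. **Population.** State that the adverse event and SAE definitions apply to all randomised participants in both arms, whether or not the intervention has been given.
3. **Triage.** State that each triage of an issue in line with the exclusion criteria, including emergent imminent suicide risk and acute protection risk, is entered in the safety register and assessed under the event definitions, whichever of the two routes is used.

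The clinical response to the participant does not change. The cost is one register entry per triage and a somewhat higher count of adverse events and SAEs. That increase should be explained when results are set beside trials with narrower definitions.
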